#### 4.5.2. Metabolic Variables

In addition to the metabolic flexibility outcomes described in Section 2.4, the participant’s body composition will be monitored. Briefly, the body composition of the individuals will be analyzed as follows: (i) a dual-energy X-ray absorptiometry (DXA) device (GE Healthcare, Madison, WI, USA) will be used to assess bone mineral density and total musculoskeletal mass by segments; (ii) a BIA device SECA mBCA 525 (SECA, Hamburg, Germany) will be used to evaluate total body water, intracellular, and extracellular water, as well as phase angle; and (iii) an air displacement plethysmograph (BodPod, COSMED, Rome, Italy) will be used to assess body fat mass for each participant. ISAK Level 2 and Level 3 certified anthropometrists will conduct the body measurements using certified equipment (Smartmet, Guadalajara, Mexico).

#### 4.5.3. Epigenetic Variables

To measure circulating microRNAs, peripheral venous blood samples will be collected in EDTA vacutainer tubes (5 mL). Subsequently, the mirVana™ miRNA Isolation Kit (Thermo Fisher Scientific, Waltham, MA, USA) will be used to analyze 14 microRNAs involved in inflammatory processes (miR-15, miR-29c, miR-30^a^, miR-142/3, miR-181^a^), adipogenesis (miR-188-5p, miR-146b-5p, miR-103, miR-107, miR-125b), and fatty acid metabolism (miR-33, miR-335, miR-370, miR-758).

Additionally, cDNA synthesis will be carried out through the reverse transcription of the microRNAs using the TaqMan MicroRNA-RT Kit (Thermo Fisher Scientific, Waltham, MA, USA). Specifically, amplification of the microRNAs of interest will be performed using the TaqMan Universal Master Mix II with UNG reagent (Thermo Fisher Scientific, Waltham, MA, USA). The specific amplification of each microRNA will be conducted with the QuantStudio 3 system (Thermo Fisher Scientific, Waltham, MA, USA), using probes specific to each microRNA and their internal controls through the TaqMan MicroRNA Assays MTO LG chemistry (Thermo Fisher Scientific, Waltham, MA, USA). The relative quantification of expression levels will be performed using the ∆∆Ct quantification method, validated through the quantification of amplification efficiency and the construction of a dynamic range curve.

In turn, the genetic influence on anthropometric and biochemical changes after the treatments will be evaluated using TaqMan probes (Thermo Fisher Scientific, Waltham, MA, USA) through an RT-PCR system using a StepOnePlus thermocycler (Thermo Fisher Scientific, Waltham, MA, USA). The polymorphisms to be assessed will include those related to obesity (rs9939609, *FTO*), lipid metabolism (rs1799883, *FABP2*), and physical adaptation to exercise (R577X, *ACTN3*). Genotyping will be verified using positive controls corresponding to the three possible genotypes in each experiment.

Although circulating microRNAs provide valuable insights into exercise-induced epigenetic changes, it is essential to consider the challenges related to their degradation and variability in expression. To address these issues, we will implement a comprehensive strategy to ensure microRNA stability and reduce variability in the results. Blood samples will be processed promptly, within 2 to 4 h, to separate plasma or serum, minimizing the risk of degradation. Additionally, samples will be stored at ultra-low temperatures (e.g., −80 °C) to preserve the integrity of the microRNAs over time.

#### 4.5.4. Dietary and Psychological Counseling

For internal control, covariates that could influence the findings (uncontrollable variables) will be monitored, including dietary patterns, mental health, and adherence of the individuals during the trial period. The food intake of all participants will be monitored through a 24 h quantitative recall of typical days (typical days before the start and at the end of the intervention), as well as a food frequency questionnaire. Food scales will be used to increase precision in food portions. Diet records will be analyzed for total calories, protein, carbohydrate, and fat intake (Diet Analysis Plus, ESHA Research, Salem, OR, USA). Dietary control will be complemented with biomarkers of nutrient intake such as urinary nitrogen and blood concentrations of cholesterol, triglycerides, and glucose.

The psychological status of the individuals will be evaluated using the validated instrument “Depression, Anxiety, and Stress Scale-21” (DASS-21), complemented by sleep-wake patterns obtained through a sleep diary and sleep quality assessment questionnaires (Pittsburgh Sleep Quality Index and Insomnia Severity Index).

Only individuals who complete at least 80% of all training sessions and measurements outlined in this intervention will be included in the data to ensure adherence to the treatments and the validity of the findings. Additionally, electronic and personal contact via text messaging will always be enabled for study follow-up.

#### 4.5.5. Data Analysis

The normality and homoscedasticity of the variables will be assessed using the Kolmogorov–Smirnov and Levene tests for each group. A student’s *t*-test will be used to analyze the differences between the pre- and post-treatment values for each variable if the data follows a normal distribution. If the data are non-parametric, the Mann–Whitney U test will be used. Statistical analysis between treatments will be conducted using ANOVA with Tukey’s post-hoc test in the case of parametric distribution and/or Kruskal–Wallis H and Dunn’s Post-hoc test for non-parametric distribution, with a Bonferroni setting for comparing intervention-induced changes. Additionally, Pearson and/or Spearman correlation tests will be used to establish associations between variables. Multivariate linear regression models will also be constructed to explore the contribution of treatment on main outcomes, which will be adjusted by potential confounder factors including age, sex, dietary variables, psychological variables, and baseline measurements. Moreover, multiple imputations will be used for generating replacement values for missing data. Statistical significance will be considered at *p* < 0.05, and all statistical analyses will be conducted using IBM SPSS package version 22 (SPSS Inc., IBM Company, Chicago, IL, USA) and GraphPad Prism v8.1 (GraphPad Software, La Jolla, CA, USA).

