We hypothesize that FatMax training, with or without resistance exercises, will significantly improve body composition (reduce body fat and increase muscle mass) and metabolic flexibility, increase fat oxidation, and alter epigenetic markers related to adipogenesis and inflammation in overweight and obese young adults. Looking to examine which biological and lifestyle factors moderate the adaptations to FatMax training, we will investigate the influence of age, sex, body fat levels, genotype, diet, psychological variables, and the type of exercise.

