## 4. Detailed Procedure

### 4.1. Sample Size Calculation

To carry out the present study, 156 young sedentary adults with overweight/obesity will be recruited through a snowball sampling. Considering the body composition changes as the primary outcome, the minimum sample size calculated for the present protocol was 44 participants to reliably detect an effect size of δ ≥ 0.5, assuming a two-sided criterion for detection that allows a maximum Type I error rate of α = 0.05 with a probability of 0.9, and considering a 20% dropout of participants, the sample size has been fixed to 52 participants per group. The statistical software used to determine the sample size was G*Power (v3.1.9.7, Universität Kiel, Düsseldorf, Germany) [15]. 

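### The between-arm test is picked from the trial data by a loosely worded pre-test rule, and neither available test is designed for unequal variances

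*Protocol article*

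**What the plan says.** Section 4.5.5 (Data Analysis) opens with "The normality and homoscedasticity of the variables will be assessed using the Kolmogorov–Smirnov and Levene tests for each group". The between-arm comparison then has two branches: ANOVA with Tukey's post-hoc test if the distribution is parametric, and Kruskal–Wallis with Dunn's test "for non-parametric distribution, with a Bonferroni setting for comparing intervention-induced changes". The branches are joined by *and/or*. Distribution is the only criterion named for choosing between them. A regression adjusted for baseline and other covariates is also planned, but only to explore the contribution of treatment.

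Three other places bear on the point:
- The Introduction states the aim "Looking to examine which biological and lifestyle factors moderate the adaptations to FatMax training", covering age, sex, body fat, genotype, diet, psychological variables and exercise type.
- Section 2.3 describes the control arm as stretching that should produce no important physiological change.
- Section 2.7 and Figure 1 exclude from analysis anyone below 75% attendance. Section 4.5.4 and Table 1 put the threshold at 80%.

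No SD is given for any outcome in any arm.

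**The concern.** The rule is stated, but it does not determine an analysis.

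- **Levene's test.** Equality of variance is a property of several groups together. Read literally, the test cannot be done group by group. Read generously, as one test across arms, its result still changes nothing in the text.
- **Choice of test.** The test is selected after seeing the data, and *and/or* permits both results for one variable. Across body composition, lipids, cytokines and 14 microRNAs, some outcomes may be judged on means and others on ranks.
- **Object of the pre-test.** Normality is assessed on the variables, while the closing clause speaks of comparing changes. On one reading the gate examines data other than those compared.
- **Unequal variances.** Tukey uses one pooled error for all three pairs. Kruskal–Wallis and Dunn also need similar spread to be read as tests of location. If trained participants respond differently from one another and controls barely change, the SD of change would be larger in A and B than in C. The pairwise error rates would then differ from nominal, in different directions for different pairs.

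**Working it through.** **Sample size used.** Section 4.1 gives "the minimum sample size calculated for the present protocol was 44 participants" "to reliably detect an effect size of δ ≥ 0.5", two-sided, with "a maximum Type I error rate of α = 0.05 with a probability of 0.9". A paired t-test with d = 0.5, two-sided α = 0.05 and power 0.90 returns n = 44, so the figure reproduces as a within-arm calculation. Inflating, 44 × 1.2 = 52.8, in line with the stated 52 per group. The checks below use 44 or 52 per arm.

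**Assumptions.** The trained:control SD ratio is not in the document. Ratios of 1.25, 1.5 and 2 were examined (A and B equal, C = 1). Uneven analysed arm sizes are also assumed.

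**Tukey's pairwise size, 52 per arm, no true differences.**
- Critical value: c = q(0.95; 3 groups, 153 df)/√2 = 2.367. Nominal size per pair is 2·P(T > 2.367) = 1.92%.
- Pooled variance: MSE = (σA² + σB² + σC²)/3.
- Ratio of true to pooled standard error: r = √[(σi² + σj²)/(2·MSE)].
- Actual size ≈ 2·P(Z > c/r).

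For ratio 1.5, MSE = (2.25 + 2.25 + 1)/3 = 1.833.
- A v B: r = √(4.5/3.667) = 1.108, c/r = 2.136, size 3.3%.
- A v C and B v C: r = √(3.25/3.667) = 0.941, c/r = 2.514, size 1.2%.

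| SD ratio | A v B, formula | A v B, simulated range | v control, formula and simulation |
|---|---|---|---|
| 1.25 | 2.6% | up to 3.0% | 1.4–1.5% |
| 1.5 | 3.3% | 3.3–3.4% | 1.2–1.3% |
| 2 | 4.0% | 3.8–4.0% | about 1.0% |

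Even with a control SD of zero, A v B cannot exceed about 5.3%. At 44 per arm and ratio 1.5, simulation gives A v B 3.3–3.4% and comparisons with control 1.3–1.4%.

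**Familywise error, Tukey.**
- Equal arms: 5.1–5.2%.
- Arms of 36/36/50 (more variable arms smaller): 6.0%, 6.3% and 7.5% at ratios 1.25, 1.5 and 2.
- Arms of 50/50/36: 4.2–4.7%.

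**Rank branch.** At ratio 2, Dunn gives A v B 2.9% (about 1.7% with equal variances) and familywise error 4.8% at 52 per arm. Familywise error is 6.1% at 36/36/50.

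**Power.** The loss depends on the pattern. If only B is more variable (SD 1/1.5/1, 44 per arm), Tukey's power for A v C at a difference of 0.5 falls from about 49% to 32%. Games–Howell keeps 48–49%.

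**Chance switching.** With truly normal data, three independent group-wise normality tests at 5% give 1 − 0.95³ = 14.3% chance of at least one false rejection. Whether one failing arm switches the test is not stated.

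**After the fix.** Games–Howell at 52/52/52 and 36/36/50, ratios 1.25–2: per-pair size 1.7–2.1% and familywise error 4.6–5.2%.

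**The case against.** Several objections are fair.

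- **A fallback for unequal variances is often left to the SAP.** This stands: the absence of Welch or Games–Howell would not by itself be a finding in a condensed article. But the article states a gate, and the defects lie in that gate.
- **Failing either check may be meant to lead to the rank tests.** This is possible, though the text names only distribution. Simulating Levene rejection as the route to Dunn gives familywise error of 4.8–4.9% with equal arms and 5.7–5.9% at 36/36/50. A v B still runs at 2.7–2.9% with equal arms, so the imbalance between pairs shrinks but remains.
- **The Bonferroni clause may govern all pairwise comparisons of change.** With a pooled variance, ratio 1.5 and 44 per arm, any-pair error is then 4.5%. That limits the overall error. It does not say which test is used.

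A reader might also infer more than the documents support:
- *That the protocol itself predicts unequal variances.* It plans to study moderators and gives no SD. Greater spread in the trained arms is an inference from the Introduction and Section 2.3.
- *That any comparison involving a more variable arm is too liberal.* When A and B both vary more than C, their comparisons with C are too conservative. Only A v B is liberal.
- *That the trial's overall false-positive rate is inflated.* With the planned equal arms it is not.
- *That mild skewness would usually trip the gate.* For a lognormal variable with sigma 0.3 and 44 per arm, at least one arm fails in about 66–68% of trials with the Lilliefors-corrected test, but in about 3–4% with the uncorrected one. The article does not say which is meant, so neither figure can be relied on.

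**Conclusion.** The point holds in a limited form. As written, Section 4.5.5 lets the data choose between a mean and a rank comparison, includes a variance test that cannot be run as described and leads nowhere, and allows both results for one variable. These defects rest on the text alone.

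The numerical consequence depends on assumed SD ratios of 1.25–2. With equal arms it is a misallocation of error between pairs. A v B, which isolates the addition of resistance training, runs at about 1.4–2.1 times its nominal size, and the comparisons with control at about 0.5–0.8 times. Familywise inflation also requires attendance exclusions to fall more heavily on the more variable arms, which is possible but not stated. The planned regression does not settle the matter while it remains exploratory. The change should be made, but the size of the error does not make it critical.

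**What to change.** In Section 4.5.5:

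1. Delete the Kolmogorov–Smirnov/Levene gate and the *and/or*.
2. Name one between-arm analysis of change in advance that is valid under unequal variances. One option is a linear model adjusted for baseline with heteroscedasticity-consistent (HC3) standard errors, which builds on the regression already planned. The other is Welch's ANOVA with Games–Howell pairwise comparisons. Choose one and write it down.
3. Keep Kruskal–Wallis and Dunn as sensitivity analyses.

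This is one paragraph of wording, with no effect on data collection. If variances are in fact equal, power at a difference of 0.5 SD with 44 per arm is about 48.8% with Games–Howell against 49.5% with Tukey, a loss of 0.7 percentage points. The HC3 model was not simulated, so that cost applies to the Games–Howell option only.

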### 4.2. Randomization and Blinding

The protocol involves the assignment of 52 subjects to one of three groups. Group A will comprise participants performing low-intensity training sessions within their FatMax zone. Group B will comprise participants who will perform both FatMax zone exercises as well as muscular resistance exercises (MRE). Both groups will be compared to group C, where participants will maintain their physical activity following an isoenergetic diet, evaluated through 24 h dietary records every four weeks.

For groups A and B, subjects will be allowed to perform their FatMax training on a treadmill or stationary bicycle, whichever is of their preference. The random sequence for participant assignment will be coded with SPSS 22 Software, looking for an equal distribution of both genders, BMI (overweight (≥25 and <30 kg/m^2^) and obesity grade 1 (≥30 and <35 kg/m^2^). All the evaluations and training sessions will be conducted in the Conahcyt National Laboratory of Body Composition and Energetic Metabolism (LaNCoCoME). The general process is shown in Figure 1.

To ensure single blinding, a researcher external to this study will enter data into the software on separate datasheets so that these researchers can analyze them without having access to treatment assignment information, storing all participant files in numerical order in a secure and accessible location. All files will be retained for a period of five years.

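### Unadjusted pre-post tests on the primary outcome stand beside an adjusted between-arm comparison, nothing says which one decides the trial, and the sample size fits only the pre-post test

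*Protocol article*

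**What the plan says.** - **Hypothesis (section 1).** "We hypothesize that FatMax training, with or without resistance exercises, will significantly improve body composition". The sentence does not say compared with what.
- **Comparator (section 4.2).** "Both groups will be compared to group C". The sentence does not link this comparison to a particular test.
- **Primary outcome and size (section 4.1).** "Considering the body composition changes as the primary outcome", the calculation arrives at a minimum of 44, chosen "to reliably detect an effect size of δ ≥ 0.5". The error rate is two-sided 0.05 and the power 90%. A 20% dropout allowance then gives 52 per group. The test behind the 44 is not named.
- **Analysis (section 4.5.5).** There are three layers. First, a Student's t-test that "will be used to analyze the differences between the pre- and post-treatment values for each variable if the data follows a normal distribution", with assumptions checked group by group. Second, "Statistical analysis between treatments will be conducted using ANOVA with Tukey’s post-hoc test in the case of parametric distribution", or Kruskal–Wallis with Dunn's test, with a Bonferroni setting for comparing the changes. Third, "Multivariate linear regression models will also be constructed to explore the contribution of treatment on main outcomes". A single threshold of p < 0.05 closes the section. No layer is named as the primary analysis.

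**The concern.** A pre-post test inside one arm uses no control data. It mixes any effect of training with whatever else changes over 16 weeks in trial participants: taking part, diet, season, regression to the mean. Only the difference between randomised arms isolates the training.

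The plan contains both kinds of test and does not rank them. The hypothesis as worded would be met by a significant change in A or B alone. The adjustment for multiple testing is attached to the between-arm step; the pre-post tests carry none. If the two disagree, the plan does not say which result stands. That disagreement is a realistic prospect, because on the stated inputs the pre-post test has 90% power and the comparison with C has much less.

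**Working it through.** **Inputs.** From section 4.1: standardised effect 0.5, two-sided α = 0.05, power 0.90, minimum 44, 52 per group after dropout. From section 4.5.5: the tests and the p < 0.05 threshold. Assumed: one normally distributed outcome, effects expressed in SD of the change score, and a shared change of 0 to 0.5 SD.

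**1. Which test gives 44?** Noncentral-t or F power at the stated inputs:

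- Paired (one-sample) t-test, two-sided: n = 43.995, so 44. Power is 0.9000 at 44 and 0.893 at 43. This matches.
- Paired, one-sided: 35.7, so 36.
- Two-sample, two-sided: 85.03, so 86 per arm.
- Two-sample, one-sided: 69.2, so 70 per arm.
- Three-group ANOVA: about 54 in total for f = 0.5, about 206 in total for f = 0.25.

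Of the designs tried, only the two-sided paired test returns 44. Nor is 44 a total for three equal arms, since 44/3 = 14.67.

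**2. Power of the comparison with C at the planned size** (two-sample t-test, effect 0.5):

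| Per arm | α = 0.05 | α = 0.05/3 |
|---|---|---|
| 44 | 64% | 47% |
| 52 | 71% | 55% |

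For 90% power the contrast needs 86 per arm at 0.05, 101 at 0.025 (two comparisons with C) and 110 at 0.05/3 (three pairwise comparisons), all before dropout.

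**3. What the pre-post test does when training has no effect.** Let all three arms share the same true change, with 44 per arm. Let p be the power of the one-arm test. Then P(A or B significant) = 1 − (1 − p)², and P(A or B significant, C not) is that value times (1 − p).

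| Shared change (SD) | p | A or B | A or B, not C |
|---|---|---|---|
| 0 | 0.050 | 0.098 | 0.093 |
| 0.1 | 0.099 | 0.188 | 0.170 |
| 0.2 | 0.254 | 0.443 | 0.331 |
| 0.3 | 0.494 | 0.744 | 0.376 |
| 0.4 | 0.737 | 0.931 | 0.245 |
| 0.5 | 0.900 | 0.990 | 0.099 |

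Simulation of 20,000 and of 40,000 trials per setting agrees: 44–45% at 0.2 SD and about 75% at 0.3 SD. In the same simulated trials the overall ANOVA stays at about 5%, and the Tukey comparisons of A or B with C at about 3.5%, whatever the shared change.

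**4. No change in any arm.** A or B is pre-post significant in about 9.75% of trials (1 − 0.95²). Counting the between-arm test as a further route gives about 11–12%. This part is ordinary multiplicity over two arms and counts both directions. In the favourable direction alone, the two pre-post tests give 1 − 0.975² = 4.9%. The evidence for the concern is the shared-change case, not this one.

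**The case against.** The controlled comparison is already in the plan. Section 2.1 describes a randomised controlled trial, section 4.2 names group C as comparator, and section 4.5.5 compares changes between arms with Tukey or Dunn tests and a Bonferroni setting. A hypothesis sentence often leaves the comparator to the design section. Being listed first does not make the t-test primary, and the ranking of tests can be left to an analysis plan that is not shown here. Section 2.3 describes group C's stretching as not producing meaningful physiological change, so a shared change is not certain.

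Most of this stands, and it rules out several stronger readings:

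- A reader might infer that the protocol lets a pre-post result alone establish efficacy. No sentence states that rule; the document only fails to exclude it. The 44–75% is therefore the consequence of one possible reading, not the trial's type I error rate.
- A reader might infer that the control arm gives no protection, or that every test runs at an uncorrected 0.05. The between-arm comparisons are adjusted.
- A reader might count the regression as a rival confirmatory route. It is worded as exploratory.
- A reader might take the pre-post test to be stated as paired and arm by arm, and the trial as knowingly sized on it. Both are inferences: the first from the per-group assumption checks, the second from the match at 44.

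The objection does not explain the sample size. The article itself fixes a significance test of pre-post change and gives an n that fits that test and not the comparison with C. This goes beyond detail deferred to an analysis plan.

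**Conclusion.** The concern holds in a limited form. Section 4.5.5 sets unadjusted pre-post tests beside an adjusted between-arm comparison and leaves open which one answers the research question. The hypothesis wording does not close that gap, and section 4.1 appears to be calculated for the pre-post test.

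With a shared change of 0.2 to 0.3 SD and no treatment effect, A or B would show a significant change in about 44% to 75% of trials (19% to 99% over 0.1 to 0.5 SD), against about 3.5% for the Tukey comparisons with C. In about 33% to 38% of trials at 0.2 to 0.3 SD, A or B would be significant and C not, the pattern most easily misread as a treatment effect. These figures rest on the assumed shared change, one normal outcome, 44 completers per arm, and a reader accepting any significant pre-post result as efficacy.

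The power figures need no assumed shared change. For an effect of 0.5 SD of change, the comparison with C has about 64% power at 44 and 71% at 52 per arm, not 90%. They take the effect size to be in SD of change and apply to an unadjusted comparison. A baseline-adjusted model could do better by an amount the document does not allow one to calculate.

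**What to change.** - **Section 4.5.5:** state that efficacy is judged only by the between-arm difference in change, with A versus C and B versus C as the primary contrasts, as section 4.2 implies, under the multiplicity adjustment already planned. B versus A can be secondary.
- **Section 4.5.5:** report within-arm changes as means with 95% confidence intervals, labelled descriptive, and keep the regression as supportive.
- **Section 1:** add to the hypothesis that the improvement is compared with group C.
- **Section 4.1:** name the test and restate the power for the between-arm contrast: about 64% at 44 and 71% at 52 per arm for an effect of 0.5 at two-sided 0.05, lower after adjustment (47% and 55% at 0.05/3). Keeping 90% at that effect would take 86 per arm before dropout, or 101 at α = 0.025. Otherwise give the effect the planned size can detect with 90% power at 0.05, roughly 0.5 × √(85/44) = 0.70 at 44 per arm and 0.5 × √(85/52) = 0.64 at 52.

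The first three changes are wording. The fourth is not only wording: the stated power becomes less favourable, and the sponsor must either accept that or recruit more. Within-arm p-values can also no longer be cited as evidence of efficacy.

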### 2.6. Duration and Timeline

This study will last for a total of 16 weeks, with assessments conducted at the beginning of this study (baseline) and after the 16-week intervention period to measure the changes in body composition, metabolic parameters, and epigenetic markers.

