### 4.5. Baseline and Follow-Up Measurements

#### 4.5.1. Biochemical Variables

Two blood samples will be collected per participant (8 mL after 8–10 h of fasting) during the clinical trial, the first on day 0 and the second at the end of the intervention (day 112). To ensure results that more accurately reflect the organism’s basal state, post-exercise biochemical measurements will be taken at least two days after the intervention, avoiding the temporary alterations caused by acute physical exertion. Plasma samples will be obtained by refrigerated centrifugation at 3000× *g* for 20 min and frozen at −80 °C until further analysis. Plasma samples will be processed for total cholesterol, high-density lipoprotein cholesterol (c-HDL), low-density lipoprotein cholesterol (c-LDL), triglycerides, glycosylated hemoglobin, and glucose by standard colorimetric procedures following the manufacturer’s instructions (Spinreact, Girona, Spain) with a Mindray BS200 biochemical autoanalyzer (MINDRAY, Shenzhen, China). Additionally, plasma IL-6 and TNF-α concentrations will be evaluated with the Quantikine immunoassay kit from R&D Systems (Minneapolis, MN, USA) and a sensitivity ELISA kit with an alkaline phosphatase signal amplification system, respectively (Quantikine HS, high sensitivity, R&D Systems, Minneapolis, MN, USA).

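### The Mann–Whitney U test, an independent-groups test, is named for non-normal pre- versus post-treatment values from the same participants; the loss of power depends on a pre-post correlation that the protocol does not give

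*Protocol article*

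**What the plan says.** Section 4.5.5 (Data Analysis) of the protocol article states that a Student's t-test "will be used to analyze the differences between the pre- and post-treatment values for each variable", provided the data are normally distributed. The next sentence gives the alternative for data that are not: the Mann–Whitney "U test will be used". Comparisons between the three arms come in a separate sentence with their own tests: "Statistical analysis between treatments will be conducted using ANOVA with Tukey’s post-hoc test", or Kruskal–Wallis with Dunn's test when the distribution is not normal.

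Section 2.6 plans "assessments conducted at the beginning of this study (baseline) and after the 16-week intervention period". Section 4.5.1 says "Two blood samples will be collected per participant", on day 0 and at the end of the intervention (day 112). Section 4.1 gives a minimum of "44 participants to reliably detect an effect size of δ ≥ 0.5", with two-sided α = 0.05 and power 0.9, raised to 52 per group for dropout. The Wilcoxon signed-rank test is not named anywhere.

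**The concern.** Pre and post values of one person are two measurements on the same unit. The Mann–Whitney U test treats them as coming from two unrelated sets of people. It therefore judges the change against the full between-person spread and ignores the fact that each person serves as their own control. When the two measurements are positively correlated, the reference distribution is too wide: the test rejects too rarely under no change and misses real changes.

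The pre/post test is planned for each variable, so any outcome that fails the normality check would be routed to this test. That could include the body-composition outcome on which the sample size is based.

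**Working it through.** **Which comparison the test belongs to.** The Mann–Whitney sentence directly follows the pre/post sentence and supplies its non-normal alternative. The between-treatment sentence comes afterwards and has its own rank test, Kruskal–Wallis with Dunn, which suits three arms. Mann–Whitney can therefore only be read as the fallback for the pre/post comparison. Sections 2.6 and 4.5.1 show that this comparison is paired.

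**Reproducing the stated 44.** Inputs from section 4.1: effect size 0.5, two-sided α = 0.05, power 0.9.
- Paired t-test, 0.5 taken as mean change divided by the SD of the change (dz). Noncentrality is 0.5·√n on n − 1 degrees of freedom. Power is 0.893 at n = 43 and 0.900 at n = 44, so the smallest n is **44**, as stated.
- Independent two-sample comparison, d = 0.5: 85 per group by the normal approximation, 86 by exact t.
- Three-group ANOVA: 207 in total for f = 0.25 and 54 in total for f = 0.5.

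Of the designs tried, only the paired test returns 44.

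**Why pairing matters.** Let each measurement have SD σ and let the pre-post correlation be ρ. The true variance of the mean change is 2σ²(1 − ρ)/n; an unpaired test assumes 2σ²/n. The standard error is thus overstated by the factor 1/√(1 − ρ): 1.83 at ρ = 0.7, 2.24 at 0.8 and 3.16 at 0.9.

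A hand approximation for an unpaired z-test with dz = 0.5 and n = 44 uses 0.5·√44 = 3.317:
- power ≈ Φ(3.317 − 1.96/√(1 − ρ))
- type I error ≈ 2Φ(−1.96/√(1 − ρ))

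At ρ = 0.5, 1.96/√0.5 = 2.772, so power ≈ Φ(0.545) = 0.71 and type I error ≈ 0.006. At ρ = 0.8, 1.96/√0.2 = 4.383, so power ≈ Φ(−1.066) = 0.14.

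**Simulation of the rank tests themselves.** Bivariate normal data, n = 44, dz = 0.5, 5,000 replicates per setting. The correlation is an assumption, because the documents state none. Simulation error is about 0.01.

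| Assumed ρ | Mann–Whitney power | Signed-rank power | Mann–Whitney type I error |
|---|---|---|---|
| 0 | 0.90 | 0.89 | 4.8% |
| 0.3 | 0.80 | 0.90 | 2% |
| 0.5 | 0.67 | 0.89 | 0.6% |
| 0.7 | 0.36 | 0.88 | 0.1% |
| 0.8 | 0.15 | 0.88 | about 0 |
| 0.9 | 0.01 | 0.89 | about 0 |

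The type I error of the signed-rank test stays near 5% throughout. With lognormal data, Mann–Whitney power is nearly the same (0.80, 0.66, 0.37, 0.16 and 0.01 at ρ = 0.3 to 0.9), while signed-rank power is 0.85 to 0.87. Skewness, the situation in which this branch would be used, does not rescue the unpaired test.

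**The case against.** A reader might infer that most of the power is lost, or that the type I error is always below 0.1%. The documents do not support either as a general statement, because no pre-post correlation is given. At ρ = 0.3 to 0.5 power falls to 0.80 and 0.67, which is a real loss but not most of it. More than half is lost only above a correlation of roughly 0.65. High correlation is plausible for fat or muscle mass over 16 weeks, but that is an assumption, and nothing in the documents supports it for cytokines or microRNAs. Which outcomes will be non-normal is equally unknown.

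The steep fall also depends on scaling. Holding dz at 0.5 means that the raw change shrinks as ρ rises: 0.5·√(2(1 − ρ)) is only 0.22 outcome SD at ρ = 0.9. If the change is instead fixed at 0.5 outcome SD, Mann–Whitney power is about 0.67 at ρ = 0.5 (where the two scalings coincide), 0.70 at 0.7 and 0.8 at 0.9. Section 4.1 does not say which SD scales δ; that it is dz is inferred from the match to 44. The point stands, but it does not overturn the comparison: signed-rank power on that scaling runs from 0.89 to 1.00.

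The scope is also limited. In a three-arm randomised trial the treatment effect rests on the between-treatment tests and the baseline-adjusted regression, which this error does not touch. With positive correlation the error is conservative, so it does not create false claims of change.

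Finally, one might count two further errors: the t-test is not labelled paired, and normality is to be checked on the variables without saying whether these are raw values or changes. Both are condensed wording. The reference to pre/post differences and the figure of 44 already point to a paired t-test. Neither is a separate finding.

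What the objection does not remove is the test name. This is not detail left to another document: the article names a test that does not fit the comparison to which it assigns it.

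**Conclusion.** Wrong as written. Section 4.5.5 assigns an independent-samples rank test to paired data, against the paired design that the stated sample size implies. For any positive pre-post correlation the test is conservative and less powerful than it should be. The loss ranges from modest (0.80 against about 0.90 at ρ = 0.3) to nearly total (0.01 against 0.89 at ρ = 0.9). These figures assume n = 44, dz = 0.5 and the stated range of ρ. The effect is confined to within-group pre/post comparisons that go down the non-normal branch, and the conclusions between treatments are unaffected.

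**What to change.** In section 4.5.5, replace the Mann–Whitney U test with the Wilcoxon signed-rank test on within-person differences (post minus pre), and in the same sentence call the t-test paired for clarity. A possible wording is: pre- and post-treatment values will be compared within each group by the paired t-test or, if the data are not normally distributed, by the Wilcoxon signed-rank test on the within-person differences.

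The cost is one sentence. It needs no new data or visits. For scale, signed-rank power at the planned 44 is about 0.88 to 0.90 under normality; reaching 0.90 by the usual efficiency ratio would take 44/0.955 ≈ 46, which is below the 52 to be enrolled per group.
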